### Sample size

The primary outcome of this trial is pain intensity during the introduction of a posterior portal. In a pilot study using five subjects for each group, pain intensity was 0 in one patient from group C5–7 and three patients from group C5–8. A pain intensity of 1 was reported by four patients from group C5–7 and two patients from group C5–8. No patient reported a pain intensity of 2. Based on the above results, alternative multinomial distributions (percentage of pain intensity of 0, percentage of pain intensity of 1, percentage of pain intensity of 2) were set as (20%, 80%, 0%) and (60%, 40%, 0%). Using 3000 Monte Carlo samples from the null multinomial distributions (33.3%, 33.3%, 33.3%) and (33.3%, 33.3%, 33.3%) and the alternative distributions, the sample size for this study was calculated to achieve a statistical power of 90% to detect a 0.4 difference in mean pain intensity between the two groups at a significance level of 0.05 using a two-sided Mann–Whitney–Wilcoxon test. Considering a dropout rate of 10%, 37 subjects are required in each group. PASS (version 15.0.3, NCSS, LLC. Kaysville, Utah, USA, ncss.com/software/pass) was used to estimate the sample size.

### Statistical analysis

The data will be analyzed in an intention-to-treat manner, and missing values will be imputed with the last observation carried forward for longitudinal variables, median of the non-missing values for non-longitudinal continuous variables, and mode of the non-missing values for categorical variables. The normality of continuous data will be determined by a Kolmogorov–Smirnov test. Normally and non-normally distributed data will be presented as the mean with standard deviation and median with first to third quartiles, respectively. Ordinal data will also be presented as a median with first to third quartiles. Categorical data will be presented as the number of patients and the percentage [27].

The primary outcome (pain intensity during the introduction of a posterior portal) will be compared between the two groups with a Mann–Whitney–Wilcoxon test. To compare the secondary outcomes between the two groups, independent-samples Student’s *t*-tests will be used for normally distributed continuous data, while Mann–Whitney–Wilcoxon tests will be used for non-normally distributed or ordinal data. Categorical data will be compared between the two groups using Pearson’s chi-square test. Paired samples Student’s *t*-tests or Wilcoxon-signed rank tests will be performed to compare normally or non-normally distributed data that are collected before and 30 min after ISBPB. Generalized estimating equations will be used to model changes in NRS scores over time and subsequently to investigate between-subject, within-subject, and interaction effects. All statistical tests are two-sided, and a level of significance <0.05 is considered statistically significant. The statistical analysis will be performed using IBM SPSS Statistics software (version 25, IBM Corp., Armonk, NY, USA) by a statistician who is not involved in data collection.

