Ipsilateral hemidiaphragmatic excursion, bilateral pupil sizes, and pulmonary function are measured in a supine position before and 30 min after the placement of ISBPB. By placing a 1.8 to 5.7 MHz convex phased array transducer (UST-9130, Hitachi Aloka Medical, Ltd.) on the ipsilateral subcostal area, the hyperechoic line of the diaphragm, which moves with the respiratory cycle, is visualized using the liver or spleen as an acoustic window. By tracing the movement of the diaphragm under real-time M-mode ultrasonography, the hemidiaphragmatic excursion is measured as the peak amplitude caused by a deep and quiet inspiration from the resting expiratory position [21]. Hemidiaphragmatic paresis and paralysis are defined as a reduction in hemidiaphragmatic excursion by 25% to 75% and by more than 75% from the baseline, respectively [22].

The stellate ganglion block is confirmed by the development of Horner’s syndrome. As Horner’s syndrome is defined as an ipsilateral pupil diameter that is less than the contralateral pupil diameter by more than 5 mm [23], we measure bilateral pupil diameters 3 min after patients are adapted to low mesopic conditions [24]. Briefly, patients are instructed to focus on the ceiling of the operating room with the eye not being tested. Patients are asked to keep the head straight and both eyes wide open with minimal blinking during targeting and measurement. An automated monocular infrared pupillometer (VIP™-200 pupillometer, NeurOptics Inc., Irvine, CA, USA) is positioned at a right angle to each patient’s axis of vision, with any tilting of the instrument minimized. Average pupil diameter and standard deviation are calculated from the pupillary data sampled at 60 frames per 2 s. The eye contralateral to the site of ISBPB is tested first and then the other eye is tested.

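### Carrying the last observation forward fills a missing 30-minute diaphragm, pupil or spirometry value with the pre-block value and so records no block effect

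*Protocol article*

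**What the plan says.** The Statistical analysis section of the protocol article states an intention-to-treat analysis in which missing data are filled by "last observation carried forward for longitudinal variables". Other variables receive the "median of the non-missing values for non-longitudinal continuous variables, and mode of the non-missing values for categorical variables". The article does not define which variables count as longitudinal, and it makes no exception for values taken before the block.

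The Measurements section fixes the time points: "Ipsilateral hemidiaphragmatic excursion, bilateral pupil sizes, and pulmonary function are measured in a supine position before and 30 min after the placement of ISBPB". Hemidiaphragmatic paresis and paralysis are then defined as a "reduction in hemidiaphragmatic excursion by 25% to 75% and by more than 75% from the baseline, respectively". Horner's syndrome is defined from the difference between the two pupils.

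Pain scores (NRS) are taken on admission to the recovery unit, on discharge from it, between 6 and 12 h after surgery, and at 24 h. For these, "Generalized estimating equations will be used to model changes in NRS scores over time". The pre-block and 30-minute values are compared by paired tests, and the arms by two-sample tests.

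**The concern.** Carrying a value forward is harmless only if nothing is expected to change between the carried value and the missing one. For the three before/after measures the opposite is true. The block is given between the two measurements, and its effect is what is being measured. The only earlier value is the pre-block one, so the rule replaces an unknown effect with no effect and then analyzes the result as observed data. The Discussion says that ultrasound, spirometry and pupillometry are combined in order to establish the true incidence of these side effects, and this rule works against that aim.

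The values may also be missing because of the block. Under Randomization and blinding, patients with serious events such as apnea are removed from the trial, and under Withdrawal the investigators may withdraw a patient on safety grounds. If that happened before the 30-minute tests, a patient with a block-related event would be entered with unchanged function.

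For pain scores, the protocol expects pain to emerge over the follow-up. It records the hour at which pain starts and provides for treatment at its onset. An assumption of no change does not suit that period.

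**Working it through.** **Inputs.** There are 37 patients per arm and 10% planned dropout (Sample size). The before/after measures have two time points (Measurements). The number of missing 30-minute or 24 h values is not given. I use m = 1, 2 and 4 of 37 as a range; 0.10 × 37 = 3.7, so m = 4 is about the planned dropout. Incidences and pain scores below are assumptions, because the article gives none.

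**The plan's own figure.** This point disputes no stated number, but 37 is the denominator, so I checked it. With no score of 2 expected, the primary comparison is 20% against 60% with no pain. A two-sided exact test first reaches 90% power at 33 per arm (0.901), and 33/0.90 = 36.7, rounded up to 37. The figure reproduces.

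**Before/after measures.** With the pre-block value carried forward, change = pre − pre = 0. A fall of 0% is below the 25% needed for paresis, so the patient is classed as unaffected. If the missing patients resemble the rest of the arm:

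- recorded mean change = true mean change × (37 − m)/37
- recorded incidence = true incidence × (37 − m)/37

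The factor is 36/37 = 0.973 for m = 1, 35/37 = 0.946 for m = 2, and 33/37 = 0.892 for m = 4, a shrinkage of 10.8%.

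With an assumed true incidence of 90% and m = 4, the recorded incidence is 0.90 × 0.892 = 80.3%. If all four missing values fall in one arm and both arms are truly at 90%, a spurious difference of 80.3 − 90 = −9.7 percentage points appears.

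**The same sentence read the other way.** Paresis class is categorical, and categorical variables receive the mode. If the commonest class is an affected one and imputation is applied to the class, missing patients are all counted as affected: recorded incidence = p(1 − f) + f, where p is the true incidence and f the missing share.

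| Assumed p | f | Excursion carried forward: p(1 − f) | Mode of class: p(1 − f) + f |
|---|---|---|---|
| 80% | 10% | 72% | 82% |
| 80% | 20% | 64% | 84% |
| 90% | 4/37 | 80.3% | 91.1% |

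The two readings differ by f and lie on opposite sides of the true value. The article does not say whether imputation precedes classification.

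**Pain at 24 h.** Bias in the arm mean = (m/37) × (carried score − true score). For m = 4:

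- carried 0, true 4: −0.43
- carried 0, true 6: −0.65
- carried 2, true 4: −0.22
- carried 4, true 4: 0
- carried 6, true 4: +0.22

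A patient missing only the 24 h score receives the 6 to 12 h score. A recovery-unit score reaches 24 h only if the 6 to 12 h score is missing too.

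**The case against.** A reader might infer that the rule enters pain scores from a still-numb arm as 24 h scores, records patients as pain-free, and biases late pain downward in every case. The documents do not support that. There is a 6 to 12 h assessment, no block duration is given, and nothing says that the arm is still numb then. A patient is entered as pain-free only if the carried score was 0, and the bias can be zero or upward, as shown above.

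A reader might also infer that a patient too breathless for spirometry is thereby recorded as having no paresis. Paresis is defined from ultrasound excursion, so failed spirometry does not by itself make the excursion missing.

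The sizes are assumed. The article gives no incidence of hemidiaphragmatic block, and 10% is planned overall dropout, not the share of missing 30-minute values. Those tests precede surgery, so some withdrawals would come after them. The word longitudinal could also be meant for pain scores alone. The median rule would then apply to a missing 30-minute value and the forced zero would disappear, but the article does not say so, and repeated measurement of one quantity is the ordinary sense of the word.

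Finally, the alternatives carry assumptions of their own. Analysis of complete pairs is biased if values are missing because of the effect, and it leaves out randomized patients in a plan described as intention-to-treat. Ordinary estimating equations on available data need data missing completely at random. These objections limit the size of the point and shape the remedy. They do not rescue a rule that carries a pre-block value past the block.

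**Conclusion.** The point holds for the before/after measures. On the ordinary reading of the stated rule, a missing 30-minute excursion, pupil or spirometry measurement is recorded as no change. The mean change, and the incidence derived from imputed excursion, shrink by m/37: 2.7% for one missing patient and 10.8% for four, if missing patients resemble the others. The mode rule, applied to the paresis class, can push the incidence the other way, so one sentence of the plan allows conflicting results.

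For pain scores the conclusion is narrower. The rule assumes stability over a period in which the protocol expects change, and the direction of the bias is uncertain. In both settings, treating a single filled-in value as observed understates uncertainty; I have not put a figure on that.

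Only secondary outcomes are affected. The primary outcome is rated once, at introduction of the posterior portal, and the sensory and motor grades are taken once at 30 minutes, so there is no earlier value of any of these to carry. The effect is nil if no values are missing.

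**What to change.** Remove last observation carried forward from the Statistical analysis section, and state that a pre-block value is never used in place of a post-block one.

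- **Excursion, pupil size and spirometry:** analyze patients with both values and report how many are missing in each arm, with reasons. Derive paresis, paralysis and Horner's syndrome from observed measurements, and do not impute the class by the mode. Add a sensitivity analysis that counts as affected any patient who could not complete the 30-minute test because of a block-related effect.
- **Pain scores:** fit the repeated-measures model to all observed scores without imputation. A likelihood-based mixed model is preferable, because it is valid under the weaker assumption that missingness depends only on observed data. If the estimating equations are kept, state that they assume data missing completely at random.

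The cost is a change of analysis wording and slightly fewer patients in some secondary comparisons. No new data are needed, so the change remains possible although the Trial status section reports recruitment complete. It should be fixed before the arms are compared.

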**Fig. 1 Fig1:**
[figure not shown]
The SPIRIT flow diagram: the schedule of enrolment, interventions, and assessments. t_1_ is before the placement of the interscalene brachial plexus block. t_2_ is when the interscalene brachial plexus block is placed. t_3_ is 30 min after the placement of the interscalene brachial plexus block. t_4_ is during surgery. t_5_ is on admission to the postanesthetic care unit. t_6_ is on discharge from the postanesthetic care unit. t_7_ is between 6 and 12 h after surgery. t_8_ is 24 h after surgery. * Forced expiratory volume at 1 s (FEV1) and FEV1/forced vital capacity. † Including worst numerical pain rating score.

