In the sitting position, patients receive oxygen at a rate of 2 L/min via a nasal cannula. Arterial blood pressure is monitored noninvasively at 5-min intervals. More frequent measurements are performed at the discretion of an attending anesthesiologist who is not involved in this study. If the patient complains of pain during surgery, fentanyl is administered in 50 μg increments. If arterial systolic blood pressure ≥170 mmHg or if visualization of the surgical field is impaired despite arterial systolic blood pressure <170 mmHg, nicardipine is administered in 0.25 mg increments. A hypotensive bradycardic event, which is defined as intraoperative bradycardia (a decrease in heart rate of more than 30 beats per minutes [bpm] in less than 5 min compared to the baseline heart rate or any decrease in heart rate to less than 50 bpm at any time) or hypotension (a decrease in arterial systolic blood pressure of more than 30 mmHg in less than 5 min compared to the baseline arterial systolic blood pressure or any decrease in arterial systolic blood pressure to less than 90 mmHg at any time) [19], is treated with inotropes, chronotropes, or vasopressors (e.g., ephedrine, epinephrine, and atropine) at the discretion of the attending anesthesiologist.

When patients begin to feel postoperative pain, 10 ml of a solution containing 25 mg of bupivacaine and 10 μg of epinephrine is injected as a bolus into the operation site via the indwelling catheter, which is then removed. Intravenous tramadol (50 mg) is administered at more than 2-h intervals when patients report a numerical pain rating scale (NRS) score of more than 2 (0 represents “no pain” while 10 represents “the worst pain imaginable”). From the afternoon on the first postoperative day, 650 mg of extended-release acetaminophen and 2 mg of immediate-release hydromorphone are administered orally three times a day. From the second postoperative day, the dosage is changed to four times a day.

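### The only stated rule for an absent pain-onset time is median imputation, which, applied as written, would record a block that outlasts observation as an average one

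*Protocol article*

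**What the plan says.** All references are to the protocol article.

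- **Outcome.** Measurements lists, among the secondary outcomes, the hour after surgery at which pain is first felt. Each patient has one value, so it is a continuous, non-longitudinal variable. No observation window is attached to it. The worst pain score, listed just before it, is limited to the first 24 h.
- **Schedule.** In the legend to Fig. 1 the last time point, t8, "is 24 h after surgery".
- **Missing data.** Statistical analysis replaces missing values of this type with the "median of the non-missing values for non-longitudinal continuous variables". It does not say whether the median is pooled or taken within each arm.
- **Test.** The same section assigns t-tests to normally distributed continuous secondary outcomes, while "Mann–Whitney–Wilcoxon tests will be used for non-normally distributed or ordinal data". It names no censoring rule or time-to-event method.

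**The concern.** Time to first pain is a time-to-event outcome. A patient who has had no pain when observation stops has no onset hour, but that patient is informative: onset is known to lie beyond the last pain-free observation. The median of the non-missing values comes only from patients whose pain did begin. If no onset later than 24 h is recorded, a patient pain-free at 24 h would be given an onset earlier than 24 h. That patient's record could then show a worst pain score of 0 over 24 h beside an onset hour inside the same period.

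The error is not neutral between arms. The value is absent because the block lasted long, so the arm with more long blocks has more of its best results moved to the centre. At stake is the secondary comparison that speaks most directly to how long each block lasts.

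**Working it through.** **The plan's own figure.** The article states no effect or power for onset time. Its only sample-size statement concerns the primary outcome: it aims "to achieve a statistical power of 90% to detect a 0.4 difference in mean pain intensity", with distributions that "were set as (20%, 80%, 0%) and (60%, 40%, 0"%), "at a significance level of 0.05 using a two-sided Mann–Whitney–Wilcoxon test". Exact enumeration of the tie-corrected test gives power 0.905 at 30 and 0.937 at 33 per group, and 33/0.9 = 36.7 rounds up to the stated 37. That figure is not in dispute. It only supplies the number per arm used below.

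**Inputs.** From the article: 37 per arm, two-sided 5% level, last assessment at 24 h, median imputation, Mann–Whitney–Wilcoxon test. Assumed, because the article gives no onset distribution: log-normal onset times with log-SD 0.4, a range of medians, and observation of onset ending at 24 h.

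**Step 1: how many patients have no onset by 24 h.** With median m, the share is 1 − Φ(ln(24/m)/0.4).

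- m = 14 h: ln(24/14) = 0.539; 0.539/0.4 = 1.347; share 8.9%, or 0.089 × 37 = 3.3 patients.
- m = 18 h: ln(24/18) = 0.288; 0.288/0.4 = 0.719; share 23.6%, or 0.236 × 37 = 8.7 patients.

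**Step 2: effect on the comparison.** In simulations of 2,000 to 4,000 runs per setting, patients with no onset by 24 h were either ranked at 24 h or given the pooled median of the observed onsets. Both versions were tested by Mann–Whitney–Wilcoxon.

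| Assumed medians, C5–7 v C5–8 | No onset by 24 h | Power, ranked at 24 h | Power, pooled median |
|---|---|---|---|
| 8 v 10 h | 0.3% v 1.4% | 64% | 62% |
| 10 v 12.5 h | 1.4% v 5.1% | 63% | 56% |
| 12 v 15 h | 4% v 12% | about 63% | about 47% |
| 14 v 18 h | 9% v 24% | 74% | 45% |
| 16 v 20 h | 16% v 32% | 62% | 31% |

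Repeat runs agree to within about three percentage points. At 14 v 18 h the estimated difference in medians falls from 4.0 h to 0.9 h. At 8 v 10 h it barely moves (2.0 v 1.9 h).

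**Step 3: a different spread.** With log-SD 0.5 and onset 1.3 times longer in C5–8, power falls from 0.59 to 0.52 at a control median of 8 h, from 0.59 to 0.35 at 12 h, and from 0.56 to 0.21 at 16 h. The pattern is the same: the loss grows with the share of patients without onset.

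**Step 4: type I error.** With no true difference, pooled-median imputation stays near 5%. If the median is taken within each arm, the error is about 5% at a median of 8 h, 6% at 10 h and 9% at 14 h (log-SD 0.4). With log-SD 0.5 it is 9%, 21% and 51% when 8%, 21% and 36% have no onset. The inflation arises because values stacked at each arm's own median amplify a chance difference between the arms.

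**The case against.** **A reader might infer that onset is followed only to 24 h.** The article does not say so. The limit is drawn from the last scheduled time point. The Intervention section ties first pain to a bedside act with no time limit ("When patients begin to feel postoperative pain, 10 ml of a solution containing 25 mg of bupivacaine and 10 μg of epinephrine is injected as") and describes care into the second postoperative day. Recording onset after 24 h is compatible with the text. This stands, and it is why the fix begins with stating the limit. A later limit would reduce the number of patients affected without changing the problem for those who pass it.

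**A reader might infer that pain-free patients are certain to be imputed.** The rule applies to missing values, and a patient seen to be pain-free at 24 h can be regarded as an observed value above 24 h. The article never classes such patients as missing. This also stands, so the point is conditional: it concerns what happens if the only written rule is applied.

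**The coding could be left to a statistical analysis plan.** Whether Kaplan–Meier is used is indeed a detail that an article may omit. But the article does not leave absent values open. It fixes a rule for every variable of this type, and that rule does not suit a censored time.

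**A reader might infer a general inflation of false positives.** That needs a by-arm median, which the text leaves unspecified. Under the pooled reading there is none.

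**Scheduled oral analgesia might mask onset.** The article states: "From the afternoon on the first postoperative day, 650 mg of extended-release acetaminophen and 2 mg of immediate-release hydromorphone are administered orally". This could matter before 24 h only for operations late enough in the day. No surgery times are given and both arms follow the same schedule, so the documents do not support a finding here.

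**Importance.** The hypothesis concerns pain at posterior portal introduction. No benefit in duration is hypothesised, and this is one item in a long secondary list. That is correct and limits the weight of the point.

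**Conclusion.** The point holds in conditional form. The stated imputation rule is wrong for a right-censored time, and the article offers no other handling for a patient without an onset hour. Applied as written with a pooled median, it biases the difference in block duration toward zero.

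The size cannot be fixed from the documents. It is negligible if blocks wear off well before 24 h, moderate at assumed medians of 12 v 15 h, and large from about 14 v 18 h upward. These results rest on log-normal onset, a 24 h limit and pain-free patients being treated as missing.

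Only a secondary outcome is affected. The correction is worth making before unblinded analysis.

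**What to change.** Amend the analysis section in three respects:

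1. State the observation limit for pain-onset time, whether 24 h or later.
2. Exempt this outcome from median imputation.
3. Treat a patient without onset as right-censored at the last pain-free observation (the limit, or withdrawal if earlier), and compare arms by Kaplan–Meier and log-rank. Alternatively, rank patients who are pain-free at the limit above all others in the Mann–Whitney–Wilcoxon test. That alternative does not serve patients who withdraw earlier, who need censoring.

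For other single-value outcomes that keep the median rule, say whether the median is pooled. A sensitivity analysis censoring at the first scheduled oral analgesic dose is optional.

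The cost is a few sentences. Recruitment is reported complete, but this changes only the analysis. Pain-free status at 24 h should be recoverable from the 24 h assessment and the worst score over 24 h, and SPSS runs the methods.

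There are two small downsides. A median onset may not be estimable if more than half of an arm is pain-free at the limit. Under the assumed log-normal model the log-rank test is also somewhat less powerful than ranking at the limit: about 71% v 75% at 14 v 18 h in one set of runs, and 59% v 64% at 8 v 10 h, where pooled imputation gave 61%.

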Changes in pulmonary function are determined by changes in the percentage of the predictive values of the measured parameters based on the equations from the European Community for Coal and Steel [25]. Forced expired volume in 1 s (FEV1), forced vital capacity (FVC), FEV1/FVC, and peak expiratory flow rate are measured using a portable spirometer (Micro I, CareFusion, Basingstoke, Hants, United Kingdom). According to the 2005 guidelines of the American Thoracic Society and European Respiratory Society [26], patients inhale completely and rapidly with a pause <1 s at total lung capacity. With a mouthpiece in the mouth and with the lips closed around the mouthpiece, patients exhale maximally until no more air can be expelled. This maneuver is repeated three times, and the best result is taken.

Complications related with ISBPB, which will be recorded prospectively, include accidental puncture of the common carotid, subclavian, dorsal scapular, or vertebral arteries, pneumothorax, hypotensive bradycardic event, epidural and intrathecal injections, local anesthetic systemic toxicity, and neurologic complications. Patients’ satisfaction with the surgical anesthesia and postoperative analgesia is measured using a five-point Likert scale consisting of “very dissatisfied,” “dissatisfied,” “unsure,” “satisfied,” and “very satisfied”.

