Regrettably, previous studies did not consider the C8 nerve root block during ISBPB even after the universal utilization of ultrasound guidance [10, 11], which ensures the accurate placement of a local anesthetic around nerve roots. Compared to the C5, C6, and C7 nerve roots, the C8 nerve root is more difficult to visualize under ultrasonography [14–16]. However, the C8 nerve root block is worth trying because the probability of its visualization has been reported to be as high as 80% [16]. When the C8 nerve root is visualized on the first rib, the C5 and C6 nerve roots mostly coalesce into the upper trunk [31]. To obtain a view of the individual C5 and C6 nerve roots, we obliquely rotate the medial side of the ultrasonography transducer cephalad, which does not require a new skin puncture. In this way, local anesthetic can be placed around each nerve root.

In this study, we chose pain intensity as the primary outcome during the incision and insertion of an arthroscopic port on the posterior aspect of the shoulder rather than the sensory blockade corresponding to each nerve root due to the individual variation in the distribution of dermatomes on the posterior aspect of the shoulder [30, 32]. Additionally, we measure the incidence of the hemidiaphragmatic block and Horner’s syndrome, which have not been completely averted to date. To determine the exact incidence, we use a multi-modality approach with ultrasonography, spirometry, and a digital pupillometer. This is the first use of a digital pupillometer to measure the change in pupil size following ISBPB. With this equipment, we expect to determine the quantitative differences between the two techniques.

This is the first randomized controlled trial to investigate whether a C8 block during ISBPB is effective in reducing pain intensity upon an insertion of a posterior portal into the posterior aspect of the shoulder. It is expected that any positive results produced by this new technique will improve the quality of surgical anesthesia provided by ISBPB for patients undergoing arthroscopic shoulder surgery.

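### Pre-block values of diaphragm excursion, pupil diameter and spirometry are collected but not used as covariates; adjusting for them would sharpen these secondary comparisons at no cost

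*Protocol article*

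**What the plan says.** The Measurements section states: "Ipsilateral hemidiaphragmatic excursion, bilateral pupil sizes, and pulmonary function are measured in a supine position before and 30 min after the placement of ISBPB". It then sets the scale of each outcome. For spirometry, "Changes in pulmonary function are determined by changes in the percentage of the predictive values of the measured parameters". Diaphragm paresis and paralysis are graded by the percentage fall in excursion from the patient's own pre-block value. Horner's syndrome is judged by comparing the pupil on the blocked side with the other pupil.

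The Statistical analysis section compares the arms on secondary outcomes with Student's t-test for normally distributed data, "while Mann–Whitney–Wilcoxon tests will be used for non-normally distributed or ordinal data". For the graded outcomes, "Categorical data will be compared between the two groups using Pearson’s chi-square test". For data taken before and after the block it adds paired t-tests or "Wilcoxon-signed rank tests will be performed to compare normally or non-normally distributed data that are collected before and 30 min after ISBPB". The one regression-type model is kept for pain scores: "Generalized estimating equations will be used to model changes in NRS scores over time".

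In the Discussion, after describing the pupillometer, the authors write: "we expect to determine the quantitative differences between the two techniques".

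**The concern.** The only analysis tied by name to the before/30-min data is a paired test. A paired test asks whether a value moved after the block; it does not estimate how far the two techniques differ. The between-arm tests that are named take no covariate. For raw excursion and pupil diameter, the article does not say whether 30-min values or changes are to be compared.

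The pre-block value is likely to be a strong predictor of the 30-min value and is already in the dataset. Leaving it out of the between-arm model gives a wider confidence interval than necessary. It also lets a chance baseline difference between two arms of 37 pass into the estimate. At stake is the precision of the quantitative side-effect comparison, which the Discussion says it expects to deliver.

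**Working it through.** **The plan's own figure.** The Sample size section gives 37 per group. With no scores of 2 assumed, the primary outcome is binary (score 1 in 80% versus 40%), and the exact Mann–Whitney–Wilcoxon test reduces to Fisher's exact test. Its power is 88.7% at 32 per arm and 90.1% at 33; 33/(1 − 0.10) = 36.7, so 37. The figure reproduces. It rests on the primary outcome alone, so nothing below alters it.

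**Inputs.** n = 37 per arm and 1:1 allocation are from the protocol. The pre-post correlation r within arm is not in the documents and is assumed over 0.3 to 0.9. Pre- and post-block SDs are taken as equal (σ).

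**Variance of the between-arm difference**
- 30-min values only: (2σ²/n) × 1
- change scores: (2σ²/n) × 2(1 − r)
- ANCOVA on the 30-min value with the pre-block value as covariate: (2σ²/n) × (1 − r²)

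Ratio of ANCOVA to change score: (1 − r²)/[2(1 − r)] = (1 + r)/2. Ratio of ANCOVA to 30-min values: 1 − r². CI width scales with the square root of the ratio.

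| r | vs change score: variance ratio | variance lower by | CI narrower by | vs 30-min value: variance ratio | variance lower by | CI narrower by |
|---|---|---|---|---|---|---|
| 0.3 | 0.65 | 35% | 19.4% | 0.91 | 9% | 4.6% |
| 0.5 | 0.75 | 25% | 13.4% | 0.75 | 25% | 13.4% |
| 0.7 | 0.85 | 15% | 7.8% | 0.51 | 49% | 28.6% |
| 0.9 | 0.95 | 5% | 2.5% | 0.19 | 81% | 56.4% |

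**In terms of power.** Take an assumed true difference of 0.5 SD and 37 per arm, with power = Φ(0.5/√(2v/37) − 1.96), where v is the variance factor above.

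| r | 30-min value | change score | ANCOVA |
|---|---|---|---|
| 0.3 | 58% | 44% | 62% |
| 0.5 | 58% | 58% | 70% |
| 0.7 | 58% | 79% | 85% |
| 0.9 | 58% | 99.8% | 99.9% |

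**In terms of patients, at r = 0.7.** ANCOVA on 74 patients equals a change-score analysis on 74 × 0.60/0.51 ≈ 87, or a 30-min-value analysis on 74/0.51 ≈ 145.

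**Chance imbalance.** If the arms differ at baseline by d, the expected shift in the estimate is r·d for 30-min values and −(1 − r)·d for change scores. ANCOVA removes it when the relation is linear. A change score therefore uses the baseline without fully adjusting for it.

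**Which comparator applies.** For spirometry the protocol defines a change, so the left half of the first table applies. For raw excursion and pupil diameter the scale is not stated, so either half could apply.

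**The case against.** The strongest reply is that the plan does not ignore baseline. Change in pulmonary function is a listed secondary outcome, and secondary outcomes are compared between the arms. Paresis and paralysis are graded against the patient's own baseline, and Horner's syndrome against the other eye. This stands, and it limits the point to a choice of method.

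Four stronger readings are tempting, and the documents do not support them.

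- A reader might infer that the paired tests will be used to argue that one technique changes a measure and the other does not. That would be unsound: with 80% power in each arm and no true difference, the arms would disagree 2 × 0.8 × 0.2 = 32% of the time. But nothing in the protocol bases a between-arm claim on the paired tests, or even says that they will be run separately by arm.
- A reader might take 49% as the loss. That figure needs r = 0.7 and a comparison of raw 30-min values, which the article does not specify. Against the change score defined for spirometry, the gain at the same r is 15% of variance.
- A reader might treat the quantitative side-effect difference as the trial's aim. It is an expectation voiced in the Discussion. The hypothesis in the Background concerns pain at the posterior portal, and the Discussion itself regards the two main side effects as of little clinical consequence in healthy patients.
- A reader might conclude that the planned comparisons are biased. Under randomisation they are valid without adjustment.

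Two further objections carry weight. First, equal SDs and a linear relation are doubtful for excursion, because a block that abolishes movement piles values up near zero. With unequal SDs, the gap against change scores can be larger or smaller than tabulated. Second, an analysis plan that is not shown may add covariates. The point therefore rests on the tests that the article names, and is offered as a better method than those, not as an omission.

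**Conclusion.** The point holds as a free improvement on secondary outcomes. No between-arm test named in the protocol uses the pre-block value as a covariate, and the paired tests do not compare the techniques. The cost is precision. Against change scores, ANCOVA cuts the variance by 35% to 5% as r runs from 0.3 to 0.9. Against raw 30-min values, if those were used, it cuts it by 9% to 81%. All of these figures rest on an assumed r, and the change-score figures also on equal pre- and post-block SDs.

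Because r is unknown, ANCOVA is the safer choice to fix in advance. With a linear relation it is never less precise than either alternative, apart from one degree of freedom, whereas each alternative does poorly in part of the range. The validity of the unadjusted comparisons, the primary analysis and the total of 74 are not in question.

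**What to change.** In Statistical analysis, for the continuous values of excursion, FEV1, FVC, FEV1/FVC and peak flow (spirometry in percent predicted) and pupil diameter, state that:

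- the arms are compared by ANCOVA on the 30-min value, with group and pre-block value as terms, and the adjusted difference is reported with its 95% CI;
- the model is checked, and a rank-based version is used if excursion values cluster near zero;
- the paired before/after tests are descriptive, and no between-arm statement rests on them.

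The protocol's change scale can be kept for presentation: with the pre-block value in the model, the group difference is the same whether the outcome is the 30-min value or the change. Leave the chi-square comparisons of paresis/paralysis and Horner's syndrome as they are, together with the primary test and the sample size.

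The cost is a few lines of analysis-plan wording. The baselines are already part of the planned measurements and standard software fits the model. Trial status reports recruitment complete, so precision can no longer come from more patients; the wording should be settled before between-arm results are seen.
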